**Fig. 3 Fig3:**
[figure not shown]
Participant data flow: Data linked to each participant was collected from several sources throughout the study period including participant-entered assessments, Fitbit and spirometer-obtained biometric data, the Epic Electronic Health Record, Wellinks, and Medicare claims data

### All feasibility outcomes will be reported descriptively

Clinical and operational efficacy will be compared across all three groups of COPD participants: full-intervention, partial-intervention, and a control group (no intervention) identified from the EMR using a novel synthetic control study strategy that has been endorsed by the FDA for generating real-world evidence [26, 27]. The clinical efficacy measures include medication requirements, healthcare utilization related to acute or urgent care, total medical expenditure, and, in the intervention arms, participant-reported outcomes (COPD severity, COPD exacerbations, patient activation measure, patient satisfaction, modified Medical Research Council Dyspnea Scale). Lastly, operational efficacy includes time spent during MIH visits, MIH visit escalation to acute care rate, and care management time.

Descriptive analysis will be used to characterize the feasibility outcomes. Continuous measures will be described using mean or median depending on the underlying distribution, and categorical variables will be described as proportions. Associations with sociodemographic characteristics and GOLD classification of COPD severity will be assessed for feasibility outcomes. Count models (Poisson, negative binomial, or zero-inflated negative binomial) will be used to compare healthcare utilization over the course of the study. Continuous models will be used to compare medical expenditure. GEE models with logit or linear link will be used to assess changes over time for COPD severity measurements. Table 5 depicts planned clinical and operational outcomes, operationalization of measurements, and preliminary analysis plans for each outcome.

**Table 5 Tab5:** Clinical and operational outcomes: A summary of chosen clinical outcomes, operationalization of measurement, analysis plan

Conceptual outcome	Operational measure	Analysis plan
Participant perceived COPD severity	• Patient Activation Measure • (Modified Medical Research Council) Dyspnea Scale	All instrument scores will be treated as continuous variables. Regression will be performed using GEE models with logit or linear link. Scores will be compared from participants at baseline and 3 and 6 months
Patient quality of life	• COPD Assessment Test • NIH-PROMIS COPD • Single Item Wellness	
Patient satisfaction	• Patient Satisfaction Measure • Study Exit Survey	
COPD-related medication changes	• Number of COPD-related medication changes during study period	Outcomes will be treated as count variables. Count models (Poisson, negative binomial, or zero-inflated negative binomial) will compare outcomes between the full-intervention, partial-intervention, and synthetic control
ED utilization	• Number of ED visits during study period	
Hospitalization	• Number of COPD-related hospitalizations during study period	
Medical expenditures	• Total claims costs during study period	Claims will be considered in aggregate for all costs paid during the study period; they will be treated as a continuous variable. Continuous models will compare outcomes between the full-intervention, partial-intervention, and synthetic control
COPD-related MIH effort	• Number of MIH visits completed • Median MIH Visit time • Median physician effort time per MIH visit	Descriptive

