Home monitoring systems using symptom reporting and wearable sensors show promise; small studies examining the use of daily symptom telemonitoring have shown that such surveillance facilitates the timely detection of COPD exacerbation [13–15]. However, the burden of daily symptoms and vital sign collection is onerous, and real-world evidence has demonstrated limited adherence to active vital sign collection that requires patient participation. Alternatively, passive collection of biometric data such as oxygen saturation and activity levels minimally adds to patient burden and has been shown to have prognostic value for acute care needs [16]. Further validation of the utility of biometric data signals as clinically actionable alerts for patients and their providers in real-world practice is needed. Additionally, early antibiotic and steroid therapy have been shown to improve both outcomes and patient quality of life, but to initiate treatment, clinicians must be alerted to clinical deterioration and be empowered to intervene promptly [10, 17]. Therefore, in tandem with the optimization of monitoring strategies, a systematic approach to review and respond to alerts based on consolidated data streams is needed to prevent added burden for the patients and their medical team. The present study has been designed to leverage ongoing efforts to configure a multimodal virtual care intervention for COPD patients and evaluate the feasibility of its implementation. Empowering patients with tools to help them expedite the recognition of worsening symptoms and removing barriers to care access are two critical components of improving clinical outcomes and patient quality of life.

The objective of the current study is to conduct a feasibility trial of the “Healthy at Home” program, a multimodal intervention aimed at preventing emergency services utilization and hospitalization among patients living with COPD. The program features a digital platform linked to a wearable health-monitoring device, virtual pulmonary support to facilitate complex care management, and access to an around-the-clock mobile integrated health (MIH) service that provides on-demand, in-home visits for evaluation and treatment of acute symptoms.

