### Virtual comprehensive pulmonary support service

All participants were presented with the option to enroll in a virtual pulmonary care program that provides multimodal support for COPD patients, through a company called Wellinks. The option to enroll in this was made available through the MyDataHelps during the first 90 days of study participation. The program includes coaching to support participant education, treatment adherence, and goal setting, and a virtual pulmonary rehabilitation program that provides a home-based exercise plan including safety instructions and COPD-specific breathing techniques. Additionally, Wellinks participants received a second equipment kit containing a spirometer, pulse oximeter, ten-foot tape measure, exercise band, and an exercise guide. The virtual pulmonary support program team coordinated introductory calls with participants to download their app and configure the spirometer and pulse oximeter devices via Bluetooth which are used to collect additional biometric data. After a comprehensive personalized assessment, a schedule for regular sessions with a health coach was created for participants. All coaching was scheduled and joined through the program’s app, with board-certified health and wellness coaches or nurse practitioners.

In the event of an acute clinical concern, the Wellinks team’s protocol was to instruct participants to contact the MIH clinician or their healthcare provider. The Wellinks team was also empowered to contact the on-duty MIH clinician directly. Participants who enrolled in the Wellinks program were classified as the “full-intervention” group, and those who enrolled in the study but opted not to participate in the Wellinks program were considered the “partial-intervention” group.

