It is expected that this study will have implications for the standard of care provided to patients at risk of admission for COPD exacerbations. If successful, increased implementation of at-home monitoring and virtual pulmonary support services may be established for patients who would benefit from this level of care. Additionally, this information can be shared with healthcare providers, such as community paramedics to assist them in providing a more proactive and robust level of care for their patients. It is also a goal of the study that these activities will help to decrease the cost acquired for patients who accumulate high levels of healthcare spending due to repeated hospitalizations and acute care needs. As a feasibility study, the current project aims to establish the impacts of study activities and expand both the population and the research partners in future analysis of this population.

By enrolling all-comers, agnostic to insurance type, residing in the towns serviced by the affiliate MIH program, it is expected that we will enroll a diverse population in reference to race, ethnicity, and socioeconomic status. However, this study is limited to those who have established health care within the system of interest and those who reside in the fairly urban areas surrounding these hospitals. Additionally, those who do not speak English are excluded from this study. Future studies should focus on a more diverse population based on geographical location and language, as there are barriers to care in those populations that will not be seen in the current study. Additionally, participants are required to have a smartphone with the ability to access the internet at home to enroll on the study app, potentially excluding a subset of the population who do not have these resources.

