## Conclusions

The Healthy at Home study’s long-term goals are to develop new tools and modes of care to better treat and understand the needs of patients with COPD. This is done by determining the feasibility of this type of digital study, as well as examining the efficacy of the multimodal interventions, across both the partial- and full-intervention groups. Furthermore, we hope to use the data gathered from this current study to inform an improved digital dashboard for use by the MIH clinical team to provide them with a more comprehensive, longitudinal history of their patients’ health. This multimodal approach may aid patients to better manage their COPD symptoms by more closely monitoring their health and providing them with multiple avenues to prevent acute care needs, including through the ability to call community-based medical providers and through regular use of the virtual pulmonary support coaching.

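### Every stated comparison with the synthetic control splits participants by their own take-up of virtual pulmonary support, so none estimates the programme as offered

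*Protocol article*

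**What the plan says.** The Introduction describes one programme, "a multimodal intervention aimed at preventing emergency services utilization and hospitalization among patients living with COPD", made up of a digital platform with a wearable, virtual pulmonary support and on-demand home visits. The Discussion likewise frames the evidence to be generated as relating to provision of that programme.

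The section on the virtual pulmonary support service explains how the two intervention groups arise. "All participants were presented with the option to enroll in a virtual pulmonary care program", and the option was "made available through the MyDataHelps during the first 90 days of study participation". Those who took it up are the full-intervention group; "those who enrolled in the study but opted not to participate in the Wellinks program were considered the “partial-intervention” group". Table 1 also marks this service as opt-in.

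The Analysis plan then states that "Clinical and operational efficacy will be compared across all three groups of COPD participants: full-intervention, partial-intervention, and a control group (no intervention"). Table 5 repeats the split for the three count outcomes (COPD-related medication changes, ED visits, COPD-related hospitalizations): "Count models (Poisson, negative binomial, or zero-inflated negative binomial) will compare outcomes between the full-intervention, partial-intervention, and synthetic control". It uses the same three groups for total claims costs. The Conclusions restate the aim as "examining the efficacy of the multimodal interventions, across both the partial- and full-intervention groups". No comparison of all enrolled participants with the synthetic control appears anywhere in the article.

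**The concern.** Take-up is a choice made after enrolment, and it is likely to be related to prognosis. People who accept coaching and exercise sessions may be more motivated, or less ill, than those who decline. The controls were never offered the service, so their records cannot show who among them would have accepted. Matching on record data can balance measured characteristics but cannot reproduce the choice itself. A full-versus-control ratio therefore mixes the programme's effect with the difference between accepters and the average patient. Partial versus control carries the opposite distortion, and full versus partial carries both.

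Timing adds to this. The option stays open for 90 days, while Table 5 counts events over the study period. As written, a participant's events before opting in can be counted in the full group, and an early exacerbation can itself influence whether the participant opts in.

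What is at stake is the clinical estimate that this pilot hands to the larger study. If the only estimates are for self-selected subgroups, the planners will have no figure for the effect of providing the programme, and the figures they do have may point in opposite directions.

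**Working it through.** The article gives no efficacy sample size, effect size or significance level, so there is no figure of the plan's own to reproduce.

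**Inputs from the article**
- Groups: full, partial, synthetic control (Analysis plan, Table 5).
- Outcomes compared across the three groups: 4 (Table 5). Participant-reported outcomes are limited to the intervention groups, and home-visit effort is descriptive.
- Enrolment benchmark 100 and adoption benchmark of at least 50% (Table 4). Taking 50% gives about 50 full and 50 partial.

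**Step 1: which contrasts exist.** For each outcome, the three groups allow full versus control, partial versus control and full versus partial. The first two describe subgroups formed by choice. The third bears on the optional service only. None is all enrolled versus control.

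**Step 2: what selection alone can do.** Let the opt-in share be p, the event rates r1 (opt-ins) and r0 (decliners), and the control rate c, with no programme effect. The enrolled mean is s = p·r1 + (1 − p)·r0. Then:
- full versus control = r1/c = (r1/s)·(s/c)
- partial versus control = r0/c = (r0/s)·(s/c)
- pooled versus control = s/c

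The factors r1/s and r0/s are the opt-in distortion. The factor s/c reflects how well the controls resemble the enrolled participants. The rates below are assumed, and controls are assumed to match the enrolled mix (c = s).

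| p | r1, r0 | s | Full vs control | Partial vs control | Full vs partial | Pooled vs control |
|---|---|---|---|---|---|---|
| 0.5 | 0.8, 1.2 | 1.00 | 0.80 | 1.20 | 0.67 | 1.00 |
| 0.5 | 0.9, 1.1 | 1.00 | 0.90 | 1.10 | 0.82 | 1.00 |
| 0.7 | 0.8, 1.2 | 0.92 | 0.87 | 1.30 | 0.67 | 1.00 |
| 0.7 | 0.9, 1.1 | 0.96 | 0.94 | 1.15 | 0.82 | 1.00 |

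The pooled 1.00 follows from setting c = s. If the controls differ from the enrolled, s/c remains in the pooled contrast and in both subgroup contrasts alike.

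**Step 3: precision.** With equal variance and nc controls (number assumed), the standard-error ratio of full versus control to pooled versus control is √[(1/50 + 1/nc)/(1/100 + 1/nc)]:
- nc = 100: √(0.030/0.020) = 1.22
- nc = 200: √(0.025/0.015) = 1.29
- nc = 1000: √(0.021/0.011) = 1.38

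For full versus partial, √[(1/50 + 1/50)/(1/100 + 1/nc)] gives √(0.040/0.020) = 1.41 at nc = 100 and √(0.040/0.011) = 1.91 at nc = 1000.

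**The case against.** The strongest defence is that this is a feasibility trial. Its leading outcomes are the Table 4 benchmarks, the clinical analyses are described as preliminary plans, and no efficacy threshold or go/no-go rule is given. The article is condensed, and an all-enrolled estimate can be obtained from the same data; nothing forbids it. Pooling is also no cure, because all enrolled participants are volunteers compared with patients found in records.

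Much of this stands, and it rules out a stronger reading. A reader might infer that the plan is at fault for naming no lead efficacy outcome or hierarchy, and that four outcomes times three pairwise contrasts leave 12 chances to claim efficacy. The documents do not support that. Ranking and multiplicity rules may sit in the full protocol or analysis plan, which are not shown. No significance level is stated. Table 5 names a three-group comparison, not pairwise tests. Four of the 12 contrasts would be full versus partial, which concern only the optional service. Likewise, the Discussion's remark that "the current project aims to establish the impacts of study activities" comes in a sentence that opens by calling this a feasibility study, so it is weak evidence of a confirmatory claim.

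The defence does not reach the split itself. The article states the grouping outright in its description of the support service, the Analysis plan, Table 5 and the Conclusions, so it is not a detail left for elsewhere. That pooling leaves selection into enrolment in place is true, but the split contrasts carry that same selection plus the opt-in distortion.

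**Conclusion.** The concern holds in this form: each stated comparison with the synthetic control is conditioned on a choice participants make after enrolment, and none estimates the programme as offered to everyone. Under the assumed rates, selection alone moves the subgroup ratios to between 0.80 and 0.94 for full versus control and between 1.10 and 1.30 for partial versus control, with no programme effect. These figures show direction and plausible scale; they are not estimates of the bias in this trial, and they assume controls that match the enrolled mix. The precision loss for full versus control, 1.22 to 1.38 times the pooled standard error, assumes 50 of 100 enrolled opt in, equal variances and 100 to 1000 controls. The feasibility outcomes are unaffected. The finding does not extend to an inflated false-positive rate or to a missing lead outcome.

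**What to change.** In the Analysis plan and in Table 5, for each of the four outcomes:

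1. Add all enrolled participants (full and partial combined, whatever their take-up of the virtual pulmonary support service) versus synthetic control as the main between-group estimate.
2. Label full versus control, partial versus control and full versus partial as exploratory. Report them as estimates with 95% confidence intervals and describe them as subject to self-selection.
3. State beside the pooled estimate that it does not remove selection into enrolment.

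The cost is one extra pooled model per outcome and a few lines of text, with no new data. The study also gives up the option of presenting an isolated favourable full-group result as the effect of the programme.

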### Recruitment

Screening for participant eligibility was performed via a query of the system’s electronic health record (EHR) for patients with a diagnosis of COPD. The number of ED visits and hospitalizations, along with the number of COPD-related medication changes in the 2 years before study enrollment, were considered proxy variables for COPD severity and treated as a count variable. We refined our recruitment to those patients that were within the second through fourth quintile of the count variable such that our cohort was comprised of patients with moderate-severity COPD. On a per-case basis, exceptions to this strategy were accommodated when patients were directly referred to the research team by the clinical team.

All participants were initially invited via email. Non-response to email solicitation was followed by two text messages within 2 weeks of the email invitation and a paper mailer sent to prospective participants’ homes. Patients who were identified as prospective participants and who were hospitalized or had upcoming ambulatory pulmonary clinic appointments were approached in person by the study team at the medical center. Finally, flyers advertising the study were placed in high-visibility places such as clinic waiting rooms. The recruitment strategy and number of participants approached are summarized in Fig. 1. Invitations for recruitment were conducted in waves ranging from 500 to 3000 patients based on the composition of the study cohort after each cycle to achieve a balanced representation of risk categories and sociodemographic factors.

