## Analysis plan

Participants are followed longitudinally for 6 months in the pilot study, during which measures of feasibility, clinical efficacy, and operational efficacy will be examined. The feasibility measures observed in the two intervention arms include the response rate for study participants, the adoption rate for virtual pulmonary support, adherence for survey and sensor data, adherence to coaching activities, ability to aggregate sensor data, and ability to measure clinical outcomes through participant-provided data. Table 4 describes planned feasibility outcomes, how they will be operationalized, and the target thresholds indicating feasibility for a larger trial. Figure 3 outlines all data collected during the study.

**Table 4 Tab4:** Feasibility outcomes: A summary of chosen study feasibility outcomes, operationalization of measurement and target thresholds for feasibility

Conceptual outcome	Operational measure	Feasibility benchmark
Recruitment	Rate of enrollment; Number of participants approached, met eligibility and enrolled	• Enrollment of 100 subjects in 12-month study period • Enroll ≥ 20% of invited participants
Retention rate	Number of enrolled participants who remain in the study 6 months	• Participant Retention ≥ 70%
Adoption of virtual pulmonary rehabilitation	Number of participants who opt in to Wellinks	• Participant adoption ≥ 50%
Wearable monitor utilization	Amount of time that participants transmit detectable biometric signals from Fitbit	• Median daily watch use ≥ 17 h • Median watch use ≥ 126 days • Median daily heart rate detection ≥ 1008 min
Completion of study instruments	Number of participants that complete each study instrument	• ≥ 80% of all required study instruments completed by participants
Data abstraction completion	Completeness of required participant clinical data from health records	• ≥ 90% completion of participant clinical data fields

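### Table 5's utilization count models name no baseline adjustment, although full versus partial intervention is the participant's own choice

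*Protocol article*

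**What the plan says.** - **Outcomes.** Table 5 defines utilization as totals: "Number of ED visits during study period" and "Number of COPD-related hospitalizations during study period". COPD-related medication changes are treated the same way.
- **Model.** The stated analysis is: "Count models (Poisson, negative binomial, or zero-inflated negative binomial) will compare outcomes between the full-intervention, partial-intervention, and synthetic control". The text introducing Table 5 calls these plans preliminary.
- **Groups.** The section on the virtual pulmonary support service says "those who enrolled in the study but opted not to participate in the Wellinks program were considered the “partial-intervention” group". The option to join was "made available through the MyDataHelps during the first 90 days of study participation". The control group comes from the EMR through a synthetic control strategy described only by citation.
- **Covariates.** The analysis text plans to examine associations with sociodemographic characteristics and GOLD class, but only for feasibility outcomes. It names no covariate, weight or offset for the count models, and it excludes none.
- **Baseline utilization.** Under Recruitment, ED visits, hospitalizations and COPD medication changes "in the 2 years before study enrollment, were considered proxy variables for COPD severity and treated as a count variable". The stated use is to choose whom to invite, with case-by-case exceptions for clinician referrals.
- **Hospitalized recruits.** The same section says: "Patients who were identified as prospective participants and who were hospitalized or had upcoming ambulatory pulmonary clinic appointments were approached in person".
- **Follow-up.** Every participant is followed for 6 months. The Table 4 retention benchmark is "Participant Retention ≥ 70" percent.

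**The concern.** The three groups in the count models are not randomized. A synthetic control, however well built, addresses participants versus controls. It does nothing for full versus partial, where the patients sort themselves. Those who take up coaching and rehabilitation may be sicker and more motivated to seek help, or fitter and more engaged, so the direction of the bias is unknown. The opt-in window also runs to day 90, so the choice can follow events that already count toward the outcome.

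The article holds an obvious adjustment variable. The 2-year count is built from the pre-enrollment versions of the three Table 5 count outcomes, and the article itself calls it a severity proxy. Hospitalization at recruitment is a second one: the Introduction puts 30-day readmission at one in five, so these patients may start at higher risk.

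At stake is what the pilot passes on. The Discussion says the study should show that a larger study of this design can produce clinical, operational and cost evidence. A confounded full versus partial estimate could mislead the decision on whether the virtual program adds anything.

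**Working it through.** **Nothing to reproduce.** The article gives no alpha, power, event rate or effect size for the count outcomes. The figure of 100 is an enrollment benchmark. The calculations below are illustrations, with assumptions marked.

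**1. Baseline difference between groups.** With no adjustment, apparent rate ratio = true rate ratio × baseline rate ratio. With a true ratio of 1:
- assumed baseline ratio 0.8: 1 × 0.8 = 0.8
- assumed baseline ratio 1.25: 1 × 1.25 = 1.25

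**2. Follow-up time.** This matters only if events after withdrawal are not captured (assumption) and the comparator is fully observed (assumption). Raw-count ratio at a true ratio of 1 = r + (1 − r) × f, where r is retention and f is the mean fraction of follow-up observed in those who leave. At the benchmark r = 0.70:
- all leave at the start, f = 0: 0.70
- leave evenly, f = 0.5: 0.70 + 0.30 × 0.5 = 0.85, or 5.1 of 6 months
- all leave at the end, f = 1: 1.00

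At r = 0.90 with even dropout the ratio is 0.95. If EHR or claims capture continues after withdrawal, it is 1.00 at any retention.

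Steps 1 and 2 can compound or offset each other: 0.8 × 0.85 = 0.68, and 1.25 × 0.85 = 1.06.

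**3. Plain Poisson.** If the variance is φ times the mean (assumption) and model-based standard errors are used, a nominal two-sided 5% test has actual error 2 × (1 − Φ(1.96/√φ)).
- φ = 1.5: 1.96/1.225 = 1.60, error 0.11
- φ = 2: 1.96/1.414 = 1.39, error 0.17

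**4. Does an offset alone suffice?** A simulation (1,500 replicates) used Poisson regression with robust standard errors. It assumed 100 participants, 200 fully observed controls, gamma frailty variance 1, 70% retention with even dropout, and counting that stops at withdrawal.
- No true effect and no baseline difference, control rate 0.3 to 1.0 events per 6 months: rejection was 9.5% to 14.5% for raw counts and 3.9% to 5.5% with a log person-time offset.
- No true effect, control rate 0.6, assumed baseline ratio 0.8 or 1.25: the offset model still rejected in 18% and 19%.

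The offset repairs exposure but not selection. This simulation compared participants with controls. It was not run for full versus partial, but the formula in step 1 applies to that contrast unchanged.

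**The case against.** The strongest reply is that the article is silent rather than wrong. It is condensed and the table is labeled preliminary. Offsets, covariates and the rule for choosing a count model normally sit in a statistical analysis plan or full protocol, and neither is shown. A reader might infer that the investigators decided against an offset and against adjustment. The text does not support that.

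Most of the further replies also stand:
- **Controls.** The comparison with controls cannot be called unadjusted, because a synthetic control may already balance utilization history.
- **Exposure.** Planned follow-up is 6 months for everyone. Fig. 3 lists the EHR and Medicare claims as data sources, and these do not depend on continued app use. The 30% loss is the limit of a benchmark, not a forecast.
- **Overdispersion.** The negative binomial and zero-inflated options show that it was foreseen.
- **Hospitalized recruits.** Consent, a shipped kit and an onboarding call come before the 6 months begin, so part of the 30-day risk window may have passed. Their number is not given.
- **The 2-year count.** It comes from a screening query. Patients who responded to a flyer or were referred may lack it, and the article does not say it exists for controls.

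None of this answers the point on full versus partial. That contrast is written into Table 5, its groups are formed by choice, and covariates are named for other outcomes in the same section but not here.

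**Conclusion.** The point holds for the full versus partial contrast: run as Table 5 is written, it confounds baseline severity with program effect. Its size depends on how those who opt in differ from those who do not, which the article cannot show. The ratios of 0.8 and 1.25 are examples.

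The stronger conclusions do not follow. The 0.85 ratio (range 0.70 to 1.00 at 70% retention) needs counting to stop at withdrawal and complete follow-up in controls. The 11% to 17% error needs plain Poisson with model-based errors and an assumed variance of 1.5 to 2 times the mean. The simulation rests on its own assumptions. None of these is a property that the document shows.

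The weight is moderate. This is a feasibility study without a stated powered efficacy test, so the feasibility conclusions are unaffected. The change is still worth making, because efficacy comparisons are planned and the main covariate already exists in the screening query.

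**What to change.** - **Adjustment.** Adjust the count models for the 2-year pre-enrollment utilization count and for hospitalized-at-recruitment status. Derive the count from the EHR for flyer and referred participants and for controls.
- **Counting window.** State that events are counted over each person's own 6 months. The words study period mean 6 months under Participant reported outcomes but 12 months in the Table 4 enrollment benchmark. Take events from EHR or claims, including after withdrawal where consent allows. Otherwise use log observed person-time as an offset.
- **Model.** Use negative binomial, or Poisson with robust variance, in place of plain Poisson.
- **Referral exceptions.** Keep them in the main analysis and examine their exclusion only as a sensitivity analysis.
- **Interpretation.** Report full versus partial as an observational contrast. Baseline covariates cannot remove selection driven by events between enrollment and an opt-in as late as day 90.

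**Cost.** A little extra EHR extraction and analysis work, and a few degrees of freedom in a sample of about 100. Recruitment and study procedures do not change.
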